In-depth interviews will be conducted with key stakeholders selected from the same primary health center area. These stakeholders may include influential figures, such as Sarpanch, Gram Panchayat Members, CMS of the tertiary healthcare institution, health insurance officers, and medical social workers. Semi-structured interview guides, prepared in Marathi and validated through pilot testing, will be utilized during these interviews. Approximately 20 to 30 in-depth interviews will be conducted until data saturation is reached, ensuring a comprehensive understanding of the participants' perspectives and experiences. Interviews will be audio-recorded with the participants' consent and transcribed verbatim for qualitative analysis. Thematic analysis will be employed to identify recurring patterns, themes, and insights related to private health insurance schemes from the qualitative data.

Outcomes

The primary objective of this study is to ascertain the extent to which residents of rural communities in Central India utilize private health insurance schemes. By examining the utilization rates, the study aims to provide insights into the current level of coverage and access to private health insurance among rural populations. This primary outcome will shed light on the effectiveness of private health insurance as a means of healthcare financing in rural settings, informing future policy decisions and interventions to improve healthcare access and affordability.

In addition to the primary outcome, several secondary outcomes will be explored. First, the study seeks to assess the level of awareness regarding private health insurance schemes among rural residents. Understanding the extent of knowledge about available insurance options will provide valuable context for interpreting utilization rates and identifying potential barriers to uptake. Furthermore, the study aims to elucidate the factors influencing individuals' decisions to utilize or abstain from private health insurance. By examining these determinants, such as economic status, education level, and perceived value of insurance, the study aims to identify targets for interventions aimed at increasing insurance coverage in rural areas.

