Another secondary outcome of interest is the exploration of participants' perceptions and attitudes toward private health insurance. Through qualitative interviews, the study will delve into individuals' beliefs, concerns, and expectations regarding health insurance, offering valuable qualitative insights into the role of insurance in healthcare-seeking behavior. In addition, the study will investigate sociodemographic determinants associated with private health insurance utilization. By analyzing factors such as age, gender, household income, and occupation, the study aims to identify demographic groups that may be particularly vulnerable to underinsurance or lack of coverage.

Statistical analysis

Quantitative data collected through the structured questionnaire will undergo a rigorous statistical analysis. Descriptive statistics, including frequencies, percentages, means, and standard deviations, will be used to summarize the characteristics of the study population and critical variables. These descriptive analyses will provide a comprehensive overview of the demographic profile of participants and their level of engagement with private health insurance. Furthermore, inferential statistics, such as chi-square tests and t-tests, will be employed to explore associations between variables and identify determinants influencing private health insurance uptake. Regression analysis may also examine the relationship between sociodemographic factors and insurance utilization, controlling for potential confounding variables. All statistical analyses will be conducted using SPSS version 29.0.2, with a predetermined significance level set at p < 0.05 to determine statistical significance.

Ethics and dissemination

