## Discussion

The proposed study seeks to investigate the utilization and determinants of private health insurance schemes in the rural communities of Central India. The findings of this study are expected to contribute to the existing literature on healthcare financing and access in rural India. Previous research has highlighted the challenges faced by rural populations in accessing affordable and quality healthcare services, with financial barriers often cited as a significant impediment [7]. Private health insurance has the potential to mitigate some of these barriers by providing financial protection against healthcare costs and facilitating access to healthcare services [8]. However, the extent rural residents utilize private health insurance and the factors influencing uptake still need to be better understood.

The anticipated findings of this study may have several important implications for policy and practice. First, by providing quantitative estimates of private health insurance coverage and awareness levels among rural populations, the study can inform policymakers about the current status of insurance penetration in rural areas. This information is crucial for designing targeted interventions to increase awareness and uptake of private health insurance schemes. For example, community-based education and outreach programs may be implemented to raise awareness about the benefits of health insurance and dispel misconceptions.

The study also aims to identify determinants influencing individuals' decisions to enroll in private health insurance or forego coverage. Sociodemographic factors such as income, education, and occupation are expected to significantly shape the insurance uptake [9]. Understanding these determinants can help policymakers design policies and programs that target vulnerable populations and address barriers to access. For instance, subsidies or incentives may be provided to low-income individuals to encourage enrollment in private health insurance schemes [10].

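### Adjusted analysis is left optional for the secondary determinants objective, so factors that merely overlap with a true determinant are liable to be reported as determinants

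*Protocol article*

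**What the plan says.** All references are to the protocol article.

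- **Committed method** (Materials and methods, Statistical analysis): "inferential statistics, such as chi-square tests and t-tests, will be employed to explore associations between variables and identify determinants influencing private health insurance uptake". The same paragraph sets the threshold, "with a predetermined significance level set at p < 0.05 to determine statistical significance".
- **Adjusted method** (next sentence): "Regression analysis may also examine the relationship between sociodemographic factors and insurance utilization, controlling for potential confounding variables". The verb changes from a commitment to a possibility, and nothing elsewhere in the article makes regression mandatory or primary for this objective.
- **Candidate factors** (Outcomes): "By examining these determinants, such as economic status, education level, and perceived value of insurance" for the decision to take up insurance, and "By analyzing factors such as age, gender, household income, and occupation" for the sociodemographic analysis. The Discussion adds an expectation: "Sociodemographic factors such as income, education, and occupation are expected to significantly shape the insurance uptake".
- **Use of the results** (Outcomes): "the study aims to identify targets for interventions aimed at increasing insurance coverage in rural areas". The Discussion gives awareness and outreach programmes, and subsidies for low-income residents, as examples.
- **Standing of the objective**: the extent of utilisation is primary. Determinants are among the secondary outcomes, although the Abstract and Conclusions name them beside utilisation as the study's aim.

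**The concern.** A chi-square test or t-test examines one factor at a time. It shows whether uptake differs between groups, not whether the factor is associated with uptake once the others are held fixed. Income, education and occupation can reasonably be expected to overlap. If income drives uptake and better-educated residents tend to have higher incomes, uptake will differ by education even when education adds nothing given income.

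This matters because the determinants are meant to select what to intervene on. A difference by education that is really a difference by income would point to another kind of programme than the one the data support. The article acknowledges potential confounders in the regression sentence, but does not commit to handling them.

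**Working it through.** **No figure to reproduce.** The article gives alpha = 0.05 and no sample size, uptake rate, effect size or correlation. Everything else below is an assumption, chosen to show a range.

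**Set-up.** Half the respondents have high income. Uptake is p1 with high income and p0 = 10% with low income. Education has no effect given income. High education is held by a share s of the high-income half and 1 − s of the low-income half, so the two education groups are of equal size and s = 0.5 means no overlap.

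**Formulas.**
- Crude uptake: a = s·p1 + (1 − s)·p0 with high education; b = (1 − s)·p1 + s·p0 with low education.
- Rejection probability of the two-sided two-proportion test with n/2 per group: Φ((|a − b| − 1.96·SE0)/SE1), plus the small opposite tail. SE0 uses the pooled proportion and SE1 the separate ones.

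**Worked case: p1 = 30%, s = 0.7.**
- Income odds ratio: (0.30/0.70)/(0.10/0.90) = 3.86.
- a = 0.7 × 0.30 + 0.3 × 0.10 = 0.24; b = 0.3 × 0.30 + 0.7 × 0.10 = 0.16.
- Crude education odds ratio: (0.24/0.76)/(0.16/0.84) = 1.66, although the odds ratio given income is 1.
- At n = 300: SE0 = 0.0462, SE1 = 0.0460; (0.08 − 1.96 × 0.0462)/0.0460 = −0.23; Φ = 0.41.

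**Milder case: income odds ratio 2.** Here p1 = 2 × (0.10/0.90) / (1 + 2 × (0.10/0.90)) = 18.2%.

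Chance that the unadjusted test flags education:

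| Income OR | Education split | Crude education OR | n = 300 | n = 400 | n = 600 |
|---|---|---|---|---|---|
| any | 50/50 (no overlap) | 1.00 | 5% | 5% | 5% |
| 2 | 60/40 | 1.15 | 7% | 8% | 9% |
| 2 | 70/30 | 1.31 | 13% | 16% | 21% |
| 3.9 | 70/30 | 1.66 | 41% | 52% | 69% |
| 3.9 | 80/20 | 2.16 | 74% | 85% | 96% |

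**Does adjustment remove the excess?** A separate simulation (1,500 runs per setting; n = 200, 400 or 800; income odds ratio 2 or 3; low-income uptake 10%; income–education correlation 0, 0.3 or 0.5) compared the chi-square test with a logistic model containing both factors. With correlation above 0, the chi-square test flagged education in 8–80% of runs. The logistic model flagged it in 4–6% in every setting. With correlation 0 both stayed at about 5%, so the excess comes from the overlap.

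**The case against.** The strongest reply has four parts.

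- **Regression is foreseen.** The article names regression for exactly this relationship, and the chi-square and t-tests are given as examples in an open list. A reader might infer that confounded factors *will* be declared determinants, or that bivariate p-values are the sole rule. The text supports neither, because regression may yet be run. What remains is that the commitment attaches to the unadjusted tests and the option to the adjusted analysis.
- **Detail may sit in an analysis plan.** Model type, covariate coding and diagnostics are fairly left there, and their absence is no fault here. Nor can one establish from this article that the decision to adjust would follow sight of the bivariate results. But the article does state which method identifies determinants and that adjustment is optional. That is a choice, not an omission.
- **One aim needs no adjustment.** The Outcomes section also seeks groups vulnerable to underinsurance. If less-educated residents have 16% uptake against 24%, they are less covered whatever the reason. A reader might take every such marginal result for a false positive; it is not, since the marginal difference is real. It misleads only when read as an independent association and used to pick a target. This part of the objection stands.
- **The size depends on assumptions.** An income odds ratio of 3.9 is a strong case, and the article nowhere says that its factors correlate, only that they are expected to shape uptake. This also stands, and is why a range is given.

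**Conclusion.** The concern holds in a limited form. The committed method does not match the question of which factors are associated with uptake given the others, and the method that does is optional. A factor overlapping with a true determinant is liable, not certain, to be reported as one.

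How often cannot be known from the article. Under the assumptions tabulated above it runs from the nominal 5% without overlap to 96% in the most extreme setting, with 7–21% in the milder ones. The direction rests only on some overlap between a true determinant and another candidate factor; the size rests on the assumed uptake, overlap and sample size.

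The primary utilisation estimate is untouched, and the crude group comparisons keep their descriptive value. As the issue concerns a secondary objective and can be put right before analysis, it is one that should be fixed rather than one that undermines the study.

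**What to change.** In the Statistical analysis section, turn the optional regression into a commitment. State that one multivariable regression of private-insurance uptake on age, gender, education, occupation and household income is the determinant analysis. Enter these factors together, without screening by bivariate p-value, and report adjusted estimates with 95% confidence intervals. Keep the chi-square tests and t-tests as descriptive comparisons, including for showing which groups lack coverage.

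The cost is one or two changed sentences, with no new data. The downside is wider intervals for correlated factors, which reflects how well the survey can tell them apart. The change should be made before the data are analysed.

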## Results

The results of the study will be drawn after the study is conducted in 2025. We expect a positive impact on the population to utilization and determinants of private health insurance schemes in the residents of rural communities in central India.

## Discussion

The proposed study seeks to investigate the utilization and determinants of private health insurance schemes in the rural communities of Central India. The findings of this study are expected to contribute to the existing literature on healthcare financing and access in rural India. Previous research has highlighted the challenges faced by rural populations in accessing affordable and quality healthcare services, with financial barriers often cited as a significant impediment [7]. Private health insurance has the potential to mitigate some of these barriers by providing financial protection against healthcare costs and facilitating access to healthcare services [8]. However, the extent rural residents utilize private health insurance and the factors influencing uptake still need to be better understood.

The anticipated findings of this study may have several important implications for policy and practice. First, by providing quantitative estimates of private health insurance coverage and awareness levels among rural populations, the study can inform policymakers about the current status of insurance penetration in rural areas. This information is crucial for designing targeted interventions to increase awareness and uptake of private health insurance schemes. For example, community-based education and outreach programs may be implemented to raise awareness about the benefits of health insurance and dispel misconceptions.

The study also aims to identify determinants influencing individuals' decisions to enroll in private health insurance or forego coverage. Sociodemographic factors such as income, education, and occupation are expected to significantly shape the insurance uptake [9]. Understanding these determinants can help policymakers design policies and programs that target vulnerable populations and address barriers to access. For instance, subsidies or incentives may be provided to low-income individuals to encourage enrollment in private health insurance schemes [10].

Furthermore, qualitative insights obtained through in-depth interviews will offer a nuanced understanding of participants' perceptions and attitudes toward private health insurance [11]. These insights can inform the design of culturally appropriate insurance products and communication strategies tailored to the needs and preferences of rural communities. By addressing concerns and misconceptions, policymakers can build trust and confidence in private health insurance schemes, encouraging greater uptake among rural residents.

## Conclusions

This study aims to comprehensively investigate the utilization and determinants of private health insurance schemes in the rural communities of Central India. Through a mixed-method approach combining quantitative surveys and qualitative interviews, the research provides a nuanced understanding of insurance coverage patterns, factors influencing uptake, and individuals' perceptions of insurance. By rigorously analyzing the data collected and interpreting thematic insights, the study seeks to offer valuable evidence for policymakers, healthcare providers, and community leaders to formulate targeted interventions to expand insurance coverage and improve financial protection against healthcare costs in rural areas. Ultimately, by disseminating the study findings widely and engaging stakeholders in meaningful dialogue, this research aspires to advance healthcare access and outcomes for rural populations in Central India, fostering a more equitable and resilient healthcare system for all.
